**Fig. 1 Fig1:**
[figure not shown]
Estimated number of included patients after recruitment. Abbreviations: *AIS* acute ischemic stroke, *TIA* transient ischemic attack, *ICH* intracerebral hemorrhage

### Eligibility criteria

Inpatients of the stroke unit will be screened for participation via the electronic health record (EHR) by study nurses after admission. They will not be involved in treatment of the patients and use set ups of the EHR to filter diagnoses and to obtain an overview of included and not included patients for minimizing losses.

### Arms and intervention

In order to implement the ICHOM-SSS into the clinical routine, it will be integrated into the medical center’s EHR to ease identification, inclusion, and storage of data. A process evaluation will be conducted, measuring the degree of feasibility in this study, acceptance of patients, clinical and administrative staff, practicability, realization, and adoption of the implementation process and execution of this assessment, reach, and fidelity to protocol (Table 1). These outcomes are chosen by means of the current standards of feasibility studies [6, 11, 18]. According to a mixed method approach, the evaluation is subdivided into quantitative and qualitative analyses. The quantitative part consists of two data quality and plausibility checks. The first analysis is conducted shortly after start of data collection, and the second is conducted after the data collection is completed.

**Table 1 Tab1:** Quantitative and qualitative feasibility assessment; type and description of analysis

Domain	Operationalisation
Acceptance	Satisfaction with the intervention and its implementation
Practicability	Relevance of the intervention and compatibility with the specific setting
Realisation and adoption	Realisation: intend and action to employ the intervention Adoption: adjusted execution of the intervention to fit the setting and recording of these adjustments
Accessibility	Penetration of intervention and access for all designated and eligible recipients
Fidelity to protocol	Quality and of intervention delivery and adherence to implementation protocol

The qualitative data are collected in semi-structured interviews with patients as well as clinical and study staff. Aim of the interviews is to capture opinion and experience of the intervieews regarding the extended health evaluation with the focus on acceptance, adequacy, and purpose as well as facilitators and barriers of the implementation process. It is planned to conduct 15 patient interviews, matched for severity of stroke impact, measured with the simplified modified Ranking Scale questionnaire (smRSq). While the patient interviews will be held by phone after the 12 months follow up is completed, the staff interviews (*n* = 5) will be conducted twice; once shortly after the introduction of the ICHOM-SSS to the clinical routine and once after the termination of the enquiry phase. The first data check and staff interview serve not only as an inspection of feasibility but allow for potentially necessary adjustments to the process. The second data check and expert interview repeat and finalize the inspection of feasibility, respectively. Interviewing professionals of different contexts and patients shall increase validity of the results by capturing various perspectives on the enquiry.

If meeting the inclusion criteria, patients will be interviewed and their clinical records analyzed during inpatient stay concerning demographics, risk factors, and patient characteristics. The interview takes place twice; once as soon as possible after intake and the second at discharge. If attending the interviews or answering the questionnaire is not possible due to disability, e.g. aphasia, the patient’s proxy will be contacted and asked to provide the information.

Assessment and parameters are collected according to the ICHOM-SSS(International Consortium for Health Outcomes Measurement (ICHOM), 2017), consisting of living situation, pre- and post-stroke functional status, cardiovascular risk factors including atrial fibrillation, the National Institute of Health Stroke Scale (NIHSS), and administrative data i.e. length of stay, survival, planned rehabilitation procedures, and discharge destination (Fig. 2). Follow up assessments take place 3 and 12 months after admission respectively. The assessment strategy is twofold. Firstly, a paper-and-pencil questionnaire is sent to the patients, consisting of a repetition of questions listed above, additional to the PROMs described below. Secondly, a short telephone interview takes place to assess the smRSq as well as record PROMs if patients were unable to fill in and send back the questionnaire themselves. If contact cannot be established postal or via three phone calls within 2 weeks patients will be excluded from further analysis.

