### Outcome measures

The primary outcome of this project is the change in patient-reported global health after stroke over the course of 1 year. This is measured three and 12 months after stroke using the Patient-reported Outcomes Measurement Information System 10-Question Short Form (PROMIS-10) questionnaire. The PROMIS-10 has been shown to be feasible and valuable in the assessment of patients after stroke [22]. Relevant domains are physical and mental health, for both used a t-score calculated from a sum-score with standardized t-values, with M ± SD = 50 ± 10, as fit in healthy American subjects. Lower values will reflect a poorer outcome. Additional information may be gained from single questions concerning participation in social activity and general health. The direction of scoring is the same. Depressive and anxiety symptoms are assessed using the Patient Health Questionnaire-4 (PHQ-4). It is a four-item score and has been established as a self-reported written questionnaire in a broad German and American cohort containing different threshold values [19]. Its scale reaches from one to six for each subdomain, with higher scores indicating worse status, and a score above 3 considered positive for a potential presence of anxiety or depression. Lastly, according to the ICHOM-SSS, we will assess motor function by the smRSq. This is done by phone interview. The smRSq has been shown to reflect motor disability with a comparable value as the traditional mRS [4]. Its scale does not differ from the latter, and reaches from zero for no symptoms, to six for death.

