Research questions 2 and 3: The data will be analysed by descriptive and inferential statistics, Depending on the outcome, (generalised) multilevel linear (patient-reported global health) and logistic (mental and motor health) regression analyses will be conducted. Factors that are believed to possibly influence the outcomes will be integrated in form of covariates. These will comprise demographics, pre-existing deficits and prior strokes, and deficits at admission (NIHSS) since recent studies have shown a negative influence of impaired motor function on different PROMIS domains(Katzan, Thompson, et al., 2018). Additionally, survival analyses (mortality) will be performed. Exploratory structural equation models are fitted to identify differential characteristic patterns of the outcomes. Further, exploratory subgroup analyses are planned, using regression models that fit the respective research questions. Results with *p* < .05 will be considered as statistically significant. As this study is of explorative nature, no adjustments for multiple testing will be made. However, the elevated risk of an occurrence of type-I errors will be regarded at the interpretation of the results. Missing values will be accounted for by using mixed modelling techniques. Sensitivity analyses will be performed when no mixed models are used. The influence of the NIHSS on the outcomes will be analysed separately using median and nonparametric tests.

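### Excluding patients after one failed two-week contact window contradicts the plan to handle missing values with mixed models, and either reading of the rule discards usable PROMIS-10 data

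*Protocol article*

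**What the plan says.** The rule on non-contact is in the protocol article under Arms and intervention, at the end of the paragraph on follow-up: "If contact cannot be established postal or via three phone calls within 2 weeks patients will be excluded from further analysis". It acts on patients, not on visits or values.

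Under Data analysis and management, the article says "Missing values will be accounted for by using mixed modelling techniques" and adds "Sensitivity analyses will be performed when no mixed models are used". The same section states: "Additionally, survival analyses (mortality) will be performed".

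Under Outcome measures, the primary outcome is the change in patient-reported global health over one year: "This is measured three and 12 months after stroke using the Patient-reported Outcomes Measurement Information System 10-Question Short Form (PROMIS-10) questionnaire". No earlier PROMIS-10 wave is described. The smRSq "reaches from zero for no symptoms, to six for death" and depends on the same contact, since "a short telephone interview takes place to assess the smRSq". Survival appears only in a list of "administrative data i.e. length of stay, survival, planned rehabilitation procedures, and discharge destination". No source is named for deaths after discharge.

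**The concern.** With two PROMIS-10 waves, a mixed model mainly helps with patients who have one wave and not the other. The exclusion rule acts on these patients, so the article gives two incompatible instructions for the same missing record.

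The sensitivity sentence does not repair this. It promises such analyses only where no mixed model is used, and the primary outcome is to be analysed with one.

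At stake is who enters the analysis of the primary outcome. If non-contact is related to health, an analysis restricted to reached patients describes a selected group, while the study aims at a broad, representative stroke-unit population. For survival, exclusion also throws away follow-up time during which the patient was known to be alive.

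**Working it through.** The article gives no figure to reproduce here. The check has two parts: the wording, then an illustration of size.

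**1. The two rules side by side**

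| Patient | Whole patient removed | Excluded from that point on | Mixed model, all available data |
|---|---|---|---|
| Reached at 3 months, missed at 12 | 3-month value discarded | 3-month value kept | 3-month value kept |
| Missed at 3 months, reachable at 12 | No data used | 12-month value lost | 12-month value used |
| Missed at both | No data | No data | No PROMIS-10 data |

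Neither reading of the exclusion matches the last column. The second row is lost on both.

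**2. Size under whole-patient exclusion**

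Assumptions, none of them from the documents except the 25%: true mean 45 at both waves (true change 0), SD 9, correlation r between waves 0.5 to 0.7, 25% lost at 12 months, log-odds of loss 0.5 to 0.8 per SD lower 3-month score. The article expects about 25% dropout but does not say that this means loss at 12 months after inclusion.

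Simulated 3-month means among reached patients are 46.08 (log-odds 0.5) and 46.62 (log-odds 0.8), so the bias B is 1.08 or 1.62. Because loss depends only on the 3-month score, the 12-month bias is r × B and the bias in the change is r × B − B = −(1 − r) × B:

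| Log-odds | r | 3-month bias | 12-month bias | Bias in change |
|---|---|---|---|---|
| 0.5 | 0.5 | +1.08 | +0.54 | −0.54 |
| 0.5 | 0.7 | +1.08 | +0.76 | −0.32 |
| 0.8 | 0.5 | +1.62 | +0.81 | −0.81 |
| 0.8 | 0.7 | +1.62 | +1.13 | −0.49 |

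Direct simulation of the 12-month means gives 45.55 to 46.12, which agrees up to simulation error. Likelihood estimation on all data gives 44.99 to 45.01. For scale, if 1040 × 0.75 = 780 patients remain, the standard error of a wave mean is 9/√780 = 0.32.

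A second illustration used n = 1040, 3-month mean 45, SD 10, slope 0.6, residual SD 8, true change +1.0 and a loss logit of −0.08 per point. With 15%, 25% and 35% unreached, whole-patient exclusion estimates the change as 0.55, 0.25 and 0.02. Likelihood estimation gives 1.00, 0.97 and 1.01.

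**3. If loss depends on the 12-month score instead**

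With the same coefficients, the two waves swap roles in the table, so whole-patient exclusion biases the change upward by 0.32 to 0.81. Likelihood estimation on all data gives a 12-month mean of 45.55 to 46.24. The 3-month mean is fully observed at 45, so its change is biased upward by 0.55 to 1.24. Keeping all data does not remove bias under this mechanism, and for the change it is no better than exclusion.

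**4. Mortality**

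Assume true 12-month mortality m = 0.15, with 20% of the living and 30%, 50% or 70% of the dead unreachable. With u_d and u_a the unreachable shares of dead and living, mortality among reached patients is m(1 − u_d) / [m(1 − u_d) + (1 − m)(1 − u_a)]. At u_d = 0.5 this is 0.075 / (0.075 + 0.68) = 9.9%. At 0.3 it is 13.4%, and at 0.7 it is 6.2%. With loss at a single wave, a Kaplan-Meier estimate that censors the same patients at the last date known alive returns the same three values.

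**The case against.** The strongest reply is that being excluded from further analysis may mean only from that point on. The sentence stands among contact procedures, not in the analysis section. On that reading, 90-day records of patients lost at 12 months stay in, the mixed model does its work for them, and the biases in the first size table do not arise. This stands as a limit on the size. It does not remove the conflict: a patient missed at 90 days is still lost at 12 months, and the text does not say which reading applies. That remaining loss was not simulated.

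The mixed-model sentence is also not empty under the exclusion, since it still covers missing forms or items among reached patients.

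Three stronger readings are tempting, and the documents do not support them:

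- **Quality of life is biased upward.** This is true of the wave means under the assumed mechanism. The primary outcome is the change, which moves downward there, and the direction reverses if loss follows the 12-month score.
- **The exclusion sentence lowers estimated mortality, for example from 15% to 9.9%.** That gap comes from deaths nobody ascertained, and censoring the same patients gives the same estimate. In-hospital deaths and deaths reported by a proxy can still be captured.
- **Mixed models would remove the bias.** That result is built into the assumption that loss depends only on the observed 3-month score.

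Finally, the study is exploratory and has no confirmatory test. That lowers the stakes but does not settle which patients are analysed.

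**Conclusion.** The article contradicts itself on patients who miss one contact. This follows from the text alone and needs no assumption. Both readings of the exclusion discard primary-outcome data that the stated method could use: 12-month values of patients missed at 90 days on either reading, and 90-day values of patients lost at 12 months on the stricter one.

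The size is illustrative and belongs to the stricter reading, with loss driven by the 3-month score. There the change is biased downward by about 0.3 to 0.8 T points, while likelihood analysis of all available data is about unbiased. The loss rate at 12 months, its dependence on health, the SD and the correlation are all assumed. No particular bias can be claimed for the study itself.

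For survival, the exclusion wrongly discards known follow-up time. Under-counting of deaths is a separate question of ascertainment.

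**What to change.** Replace the exclusion sentence with a rule that a failed contact (post, or three calls within 2 weeks) closes that visit only and is coded as missing at that visit. State that:

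- all observed PROMIS-10, PHQ-4 and smRSq values stay in the mixed models;
- the 12-month contact is still attempted after a missed 90-day contact;
- survival analyses keep unreached patients, censored at the last date known alive.

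As a separate point, check vital status through the EHR and any proxy before declaring a patient lost. Censoring alone does not recover unreported deaths, which would count as events in the survival analysis and as 6 on the smRSq.

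The cost is one sentence of wording, a repeat mailing and calls at 12 months for patients missed at 90 days, and an EHR look-up. The change removes the contradiction and the avoidable loss of data. It does not protect against loss that depends on the unobserved 12-month score, and this should be said when the results are interpreted.

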**Fig. 2 Fig2:**
[figure not shown]
Timepoints and content of determined data

### Outcome measures

The primary outcome of this project is the change in patient-reported global health after stroke over the course of 1 year. This is measured three and 12 months after stroke using the Patient-reported Outcomes Measurement Information System 10-Question Short Form (PROMIS-10) questionnaire. The PROMIS-10 has been shown to be feasible and valuable in the assessment of patients after stroke [22]. Relevant domains are physical and mental health, for both used a t-score calculated from a sum-score with standardized t-values, with M ± SD = 50 ± 10, as fit in healthy American subjects. Lower values will reflect a poorer outcome. Additional information may be gained from single questions concerning participation in social activity and general health. The direction of scoring is the same. Depressive and anxiety symptoms are assessed using the Patient Health Questionnaire-4 (PHQ-4). It is a four-item score and has been established as a self-reported written questionnaire in a broad German and American cohort containing different threshold values [19]. Its scale reaches from one to six for each subdomain, with higher scores indicating worse status, and a score above 3 considered positive for a potential presence of anxiety or depression. Lastly, according to the ICHOM-SSS, we will assess motor function by the smRSq. This is done by phone interview. The smRSq has been shown to reflect motor disability with a comparable value as the traditional mRS [4]. Its scale does not differ from the latter, and reaches from zero for no symptoms, to six for death.

### Data analysis and management

Research question 1: A process evaluation is performed to answer the first research question. This means process data on the implementation and enquiry process will be collected. Two structured analyses of process- and outcome data will be performed on congruency and completeness in order to detect potential discrepancies between conception and realization. The results of the evaluation will be examined via descriptive statistics. The interviews will be recorded, transcribed and analyzed using a realist thematic analysis approach [3], specifically a framework content analysis [9]. The thematic analysis approach is a method by which qualitative data is coded into themes. We will use a mainly deductive approach, as our feasibility outcomes are already predefined (see Table 1). Coding schemes are developed beforehand and discussed regularly. Nevertheless, we are open to the possibility of inductive theme generation, if data suggests. The results will be reported using consolidated criteria for reporting qualitative research [2].

Research questions 2 and 3: The data will be analysed by descriptive and inferential statistics, Depending on the outcome, (generalised) multilevel linear (patient-reported global health) and logistic (mental and motor health) regression analyses will be conducted. Factors that are believed to possibly influence the outcomes will be integrated in form of covariates. These will comprise demographics, pre-existing deficits and prior strokes, and deficits at admission (NIHSS) since recent studies have shown a negative influence of impaired motor function on different PROMIS domains(Katzan, Thompson, et al., 2018). Additionally, survival analyses (mortality) will be performed. Exploratory structural equation models are fitted to identify differential characteristic patterns of the outcomes. Further, exploratory subgroup analyses are planned, using regression models that fit the respective research questions. Results with *p* < .05 will be considered as statistically significant. As this study is of explorative nature, no adjustments for multiple testing will be made. However, the elevated risk of an occurrence of type-I errors will be regarded at the interpretation of the results. Missing values will be accounted for by using mixed modelling techniques. Sensitivity analyses will be performed when no mixed models are used. The influence of the NIHSS on the outcomes will be analysed separately using median and nonparametric tests.

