**Methods:**

We plan to enroll 1040 consecutive patients with the diagnosis of acute ischemic stroke, transient ischemic attack, or intracerebral hemorrhage in a prospective observational study. Demographics, cardiovascular risk factors, and living situation are assessed at inpatient surveillance. At 90 days and 12 months after inclusion, follow-up assessments take place including the Patient-reported Outcomes Measurement Information System 10-Question Short Form (PROMIS-10), the Patient- Health Questionnaire-4, and the simplified modified Ranking Scale questionnaire. The acceptance and feasibility (1) will be assessed by a process evaluation through qualitative semi-structured interviews with clinical staff and patients and quantitative analyses of the data quality evaluating practicability, acceptance, adoption, and fidelity to protocol. The primary outcome of objective 2 and 3 is health-related quality of life measured with the PROMIS-10. Additional outcomes are depressive and anxiety symptoms and patient participation in their social roles. Patient-reported outcomes will be assessed in their longitudinal course using (generalized) mixed regressions. Exploratory descriptive and inference statistical analyses will be used to find patterns of patient characteristics and predictive factors of the outcome domains.

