### Sample size estimation

In the past years, approximately 1300 patients with a relevant diagnosis were admitted at the stroke unit of our hospital annually. Of these patients, 60% had an ischemic stroke, 32% had a transient ischemic attack, and 8% were admitted with intracerebral hemorrhage. With an expected dropout of approximately 25%, we aim to include *n* = 1040 patients (Fig. 1). This number allows for exploratory descriptive and inferential analyses with high precision and power, including subgroup analyses and the use of multivariate and longitudinal models. While the planned analyses are of exploratory nature, sample size calculations, done with GPower [7] show that in order to identify a small effect (H0 ρ^2^ = 0.01 and H1 ρ^2^ = 0.05 in a two-sided test with a power of 0.90, a regression analysis with 25 predictors the analysis of data of 846 cases are necessary, which is below the expected sample size.

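### The PHQ-4 depression and anxiety subscores appear to be analysed as positive or negative by logistic regression; if so, the predictor analysis discards information that the graded scores hold, and the text should settle which model is meant.

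*Protocol article*

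**What the plan says.** Three places in the protocol article bear on this.

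- **Abstract, Methods:** "Additional outcomes are depressive and anxiety symptoms and patient participation in their social roles". The outcome named is symptoms.
- **Outcome measures:** "Depressive and anxiety symptoms are assessed using the Patient Health Questionnaire-4 (PHQ-4"). Each subdomain has a score printed as running from one to six, "with higher scores indicating worse status, and a score above 3 considered positive for a potential presence of anxiety or depression". No other PHQ-4 rule for analysis is given. The section also notes that the instrument has been established with different thresholds.
- **Data analysis and management, research questions 2 and 3:** "generalised) multilevel linear (patient-reported global health) and logistic (mental and motor health) regression analyses will be conducted". The word logistic is not qualified as binary or ordinal. It also covers motor function, measured by the smRSq from zero to six, for which no cut is stated.

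No expected share of patients above the PHQ-4 cut is given, and no continuous or explicitly ordinal analysis of the PHQ-4 is named.

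**The concern.** The analysis section sets a linear model for global health against a logistic model for mental health. The outcome section supplies one rule that turns a PHQ-4 subscore into yes or no. The natural reading of the two is that the subscore is cut at above 3 and the binary result is modelled.

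One of the study's aims is to find factors that influence outcome and its course after stroke. A cut score serves that aim poorly in two ways. All scores up to 3 count as the same, and so do all scores of 4 and over, so predictor effects are estimated with wider intervals and real predictors are missed more often. And a patient whose score falls from 6 to 4, or rises from 1 to 3, between the two follow-ups counts as unchanged. The article offers the cut as a screen for possible anxiety or depression and gives no reason for using it as the scale on which predictors are sought.

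**Working it through.** **The plan's own figures.** The article gives no figure for the PHQ-4 analysis. Its one computed figure ("a regression analysis with 25 predictors the analysis of data of 846 cases are necessary") concerns explained variance in a linear regression, so there is nothing of the plan's own to reproduce on this point.

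**Inputs from the article.** Cut at above 3; 1040 patients to be included; about 25% dropout. If dropout comes after inclusion, 1040 × 0.75 = 780 are analysable.

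**Assumptions.** A subscore from 0 to 6 (the article prints one to six); proportional odds; one predictor split 50/50 at one time point; and four score distributions, from mostly low scores to more spread out. Shares for scores 0 to 6:

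- A: .55, .17, .13, .06, .04, .02, .03
- B: .40, .18, .18, .10, .06, .04, .04
- C: .28, .17, .20, .12, .10, .06, .07
- D: .20, .15, .20, .15, .12, .08, .10

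**Step 1, efficiency.** With q the share above the cut and p_i the share at each score, the information of the binary analysis relative to the proportional-odds model is

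efficiency = 3q(1 − q) / (1 − Σp_i³).

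| | q | 3q(1 − q) | 1 − Σp_i³ | efficiency | 780 × efficiency |
|---|---|---|---|---|---|
| A | 0.09 | 0.246 | 0.826 | 0.30 | 232 |
| B | 0.14 | 0.361 | 0.923 | 0.39 | 305 |
| C | 0.23 | 0.531 | 0.962 | 0.55 | 431 |
| D | 0.30 | 0.630 | 0.974 | 0.65 | 505 |

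The last column is the number of patients who would give the same information if analysed on the full score. The efficiency itself does not depend on the 780.

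**Step 2, the threshold.** If positive meant 3 or more, q would be 0.15, 0.24, 0.35 and 0.45, and efficiency 0.46, 0.59, 0.71 and 0.76. The loss is smaller but remains.

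**Step 3, other distributions and reference models.** With the cut at above 3, a distribution with 7% positive gives efficiency 0.25 and a flat one over seven levels (43% positive) gives 0.75: a loss of 75% and 25%. For an underlying normal score, efficiency is φ(c)² / [q(1 − q)], with c the normal quantile at the cut: 0.64 at 50% positive (loss 36%), 0.49 at 20% (loss 51%), 0.34 at 10% (loss 66%). Against a linear or ordinal probit model on seven levels, the loss is about 32% to 63%.

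**Step 4, what it means for power.** For an effect that the ordinal model detects with power 0.90 at two-sided 0.05 (odds ratio 1.50 to 1.56 with 780 patients), the cut has power Φ(3.24 × √efficiency − 1.96) = 0.42, 0.53, 0.67 and 0.74. This holds for that effect size only. At an odds ratio of 2, Φ(ln 2 × √[780 q(1 − q)/4] − 1.96) gives 0.79, 0.92, 0.98 and 0.99, so strong predictors would mostly still be found.

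**The case against.** The strongest reply is that the article never says the score is dichotomised. The rule that "a score above 3 considered positive for a potential presence of anxiety or depression" can be read as an aid to interpretation, not as the definition of an endpoint. The same word, logistic, covers the smRSq, which has no stated cut, so an ordinal model may be what the authors mean; a mixed cumulative-logit model is itself a generalised multilevel logistic regression. A condensed article may also leave such detail to the full protocol or analysis plan. This stands in part: binary is the more natural reading for the PHQ-4, but it is an inference.

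The size is also open to challenge, and rightly. No score distribution or share positive is given. A reader might infer that the cut lies far in the upper tail, or that a fixed third to two thirds of the information is lost. The article supports neither: on the scale as printed, above 3 is the midpoint (1 to 3 against 4 to 6), and every figure for the loss rests on an assumed distribution. Nor does it support dividing expected positives by 25 predictors, since that number belongs to the linear sample-size calculation and is not a specification of the PHQ-4 model. The article also calls 846 below its expected sample size, so its authors may not expect as few as 780 analysable patients.

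Finally, the PHQ-4 is an additional outcome in a study declared exploratory, who screens positive is a legitimate clinical question, and the planned descriptive statistics and structural equation models are not tied to the cut. That limits the weight of the point. It does not remove it: an exploratory search for predictors is the setting in which lost information costs most, and no planned analysis is stated to use the full score.

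**Conclusion.** The point holds conditionally. As written, the article appears to analyse the PHQ-4 subscores as positive or negative, but does not say so; an ordinal logistic model is not excluded. If ordinal is meant, one word settles it. If binary is meant, the predictor analysis for depressive and anxiety symptoms loses information and is blind to change that stays on one side of the cut.

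The size rests on assumptions about a share that the article does not give: efficiency of about 0.30 to 0.65 against proportional odds with 9% to 30% positive on a 0-to-6 score, and a loss of about 25% to 75% over wider assumptions. These come from a single predictor at one time point, whereas the plan is a multilevel model over two.

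A reader might infer that the main result of the study is weakened. It is not: the primary outcome, PROMIS-10, is assigned a linear model. This is a cheap improvement to a secondary analysis.

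**What to change.** In Data analysis and management, research questions 2 and 3, state the PHQ-4 model: each subscale (depression, anxiety) is analysed on its full score with a mixed ordinal (cumulative-logit) model, using the planned covariates and the 3- and 12-month time points. Report the proportion above the screening cut at each time point descriptively, and keep the binary logistic model as a secondary analysis.

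A linear mixed model on the score is a simple alternative. In simulation with the four assumed distributions (390 per group, odds ratio 1.50 to 1.56), a t-test on the score had power 0.84 to 0.89 where a rank test had 0.89 to 0.90.

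The cost is one sentence and a different model call in R, which the article already names. No new data or patients are needed. The downside is that an ordinal odds ratio is less direct to read than screening positive and assumes proportional odds; the secondary binary model offers the direct reading and does not need that assumption.
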